### Randomization

Patients will be randomized at inclusion during hospitalization after verification of their suitability for inclusion. Patients will be randomized using the Clinsight system (ENNOV). Randomizing two cases for one control has been chosen based on the positive results of the study by Klek et al. exhibiting a higher 30-day fistula closure rate in the EN group for patients with pancreatic fistula, which has a similar context [16]. In addition, European guidelines are in favor of EN for patients needing artificial nutrition with a grade A level of evidence (without the context of PUGIF where nothing has been demonstrated to date). A dynamic randomization procedure by minimization will be performed to achieve a balance between the following prognostic factors: the type of fistula (high- versus low-output, where a high-output fistula is defined as effluent greater than 200 ml/24 h), malignant/nonmalignant disease, and somatostatin analog use. The variable of treatment center will also be considered in the minimization procedure. Taking into account the fistula outflow, stratification on the surgical procedure/organ will not be included in the minimization procedure since the two are strongly linked.

### Treatment methods

Each nutritional support will be planned to provide a similar amount of calories and proteins. According to the French guidelines on perioperative nutrition [23] the amount of calories will be 30–35 kcal/kg/day including proteins. The protein or amino acid intake will represent 18–20% of caloric intake: 1.35–1.5 g/kg/day (i.e., nitrogen at 0.21–0.24 g/kg/day).

EN or TPN will start in the first 72 h following randomization with the need for tube or catheter placement (if not already placed and according to randomization arm) in the meantime.

EN can be delivered through a jejunostomy or a nasojejunal tube. A polymeric hypercaloric hyperprotidic product without immunonutrients will be chosen. The nutritional product will be the one usually used in each center. EN will be started slowly (20 ml/h) with a progressive increase in the infusion rate every day according to the tolerance of the patient. The expected infusion rate to cover nutritional needs should be obtained in a week. If the tolerance of EN does not allow the energy and protein requirements to be met at the end of the first week it will be necessary to start a complementary parenteral nutrition to make up the nutritional requirements. EN will be infused at a continuous rate via an enteral pump. In the case of obstruction or failing of the enteral tube, a feeding tube should be replaced immediately with the agreement of the surgeon. If it is impossible to replace an enteral tube, parenteral nutrition should be started on the same day.

TPN will be delivered through a central venous access, a peripherally inserted central catheter line or a totally implantable venous access port or any other approved TPN device. The parenteral nutritional product will be chosen according to the patient’s nutritional requirements as defined in the study and according to the usual care of each center (industrial or compounding bag). However, it is recommended to avoid a parenteral formulation containing a long-chain triglyceride lipid emulsion and to add intravenous glutamine (Dipeptiven®) in the TPN [24]. If Dipeptiven® is added to parenteral nutrition (recommended dose of 0.3–0.5 g/kg/day of dipeptide), the amount of amino acids (or nitrogen) will be included in the calculated amount of protein intake. Parenteral nutrition will include electrolytes, vitamins and trace elements every day. Serum levels of phosphate should be assessed every 72 h. TPN should be infused over 24 h with a pump. In case of catheter obstruction or bacteremia related to the catheter, the central venous catheter will be replaced and complications will be treated according to guidelines [25, 26].

Patients will have appropriate care according to local procedures to avoid complications with the feeding tube or enteral venous catheter.

For all patients, glycemia will be checked regularly. In case of hyperglycemia (>10 mmol/l or >1.8 g/l), glycemia should be maintained between 7.8 and 10 mmol/l (1.4 to 1.8 g/l) with the use of insulin.

Nil-per-mouth (except a maximum of 500 ml/day of clear liquids for comfort) will be required during fistula treatment and until at least 5 days after fistula closure. After this, oral alimentation will be progressively introduced under the supervision of a nutritionist using a previously known energetic value, and the proportion of oral alimentation ingested will be monitored daily.

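### The protein range in grams (1.35–1.5 g/kg/day) equals 18–20% of calories only at 30 kcal/kg/day; over the permitted 30–35 kcal/kg/day it should run to 1.75

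*Protocol article*

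**What the plan says.** All the relevant text is in the protocol article, under Treatment methods.

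- Energy: "the amount of calories will be 30–35 kcal/kg/day including proteins".
- Protein: "The protein or amino acid intake will represent 18–20% of caloric intake: 1.35–1.5 g/kg/day". The same figure is then converted to nitrogen: "1.35–1.5 g/kg/day (i.e., nitrogen at 0.21–0.24 g/kg/day".
- Parity between arms: "Each nutritional support will be planned to provide a similar amount of calories and proteins".
- Enteral arm, after one week: "If the tolerance of EN does not allow the energy and protein requirements to be met at the end of the first week", parenteral nutrition is added to make up the difference.
- Parenteral arm: the product is selected by the patient's "nutritional requirements as defined in the study".

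The section gives no energy value per gram of protein. It does not tie the gram range to one calorie level, and it does not say which figure prevails if the two differ.

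**The concern.** The sentence presents the gram range as the equivalent of the percentage range. Energy may vary from 30 to 35 kcal/kg/day, so a fixed percentage must give a gram range that widens with it. The printed range does not widen: its width is what 18–20% gives at one calorie level.

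This is part of the dosing rule for the intervention, and two instructions rely on it. Planning similar protein in both arms needs one protein target. The week-1 check in the enteral arm needs one protein requirement, below which complementary parenteral nutrition starts. A site working from the grams and a site working from the percentage could apply different floors at the same calorie target, each believing that it follows the protocol.

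**Working it through.** **Inputs from the document (Treatment methods).** Energy E = 30–35 kcal/kg/day, proteins included; protein share s = 18–20%; printed protein 1.35–1.5 g/kg/day; printed nitrogen 0.21–0.24 g/kg/day.

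**Assumptions.** Energy factor f = 4 kcal per gram of protein; 6.25 g protein per gram of nitrogen. Neither is stated. The first is supported by step 1 and the second by step 5.

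**Formula.** Protein (g/kg/day) = s × E / f.

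**1. Reproduce the printed range.** At E = 30: 0.18 × 30 / 4 = 1.35 and 0.20 × 30 / 4 = 1.50. Both printed ends are matched exactly.

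**2. Carry the calorie range through.** At E = 35: 0.18 × 35 / 4 = 1.575 and 0.20 × 35 / 4 = 1.75. Both exceed the printed upper end. Over 30–35 kcal/kg/day the percentage therefore gives 1.35–1.75 g/kg/day.

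| E (kcal/kg/day) | 18% (g/kg) | 20% (g/kg) | 18% floor minus 1.35 | Intakes meeting both figures |
|---|---|---|---|---|
| 30 | 1.350 | 1.500 | 0 | 1.350–1.500 |
| 32 | 1.440 | 1.600 | 0.090 | 1.440–1.500 |
| 33 | 1.485 | 1.650 | 0.135 | 1.485–1.500 |
| 34 | 1.530 | 1.700 | 0.180 | none |
| 35 | 1.575 | 1.750 | 0.225 | none |

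The overlap ends where the 18% floor reaches 1.5 g/kg: E = 1.5 × 4 / 0.18 = 33.3 kcal/kg/day. Read the other way, the printed grams at 35 kcal/kg/day are 1.35 × 4 / 35 = 15.4% to 1.5 × 4 / 35 = 17.1% of energy, below the 18% minimum.

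**3. Check that the mismatch does not come from the choice of f.** The ratio of upper to lower end does not involve f. Over the full range it should be (0.20 × 35) / (0.18 × 30) = 7.0 / 5.4 = 1.296. As printed it is 1.5 / 1.35 = 1.111, which equals 20/18, so energy was held at one value. Matching both printed ends over 30–35 would need f = 5.4 / 1.35 = 4.0 at the bottom and 7.0 / 1.5 = 4.67 at the top.

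**4. Size of the floor difference.** At 35 kcal/kg/day: 1.575 − 1.35 = 0.225 g/kg/day, or 0.225 / 1.35 = 16.7% of the gram floor. For an assumed body weight of 60–80 kg this is 0.225 × 60 = 13.5 g to 0.225 × 80 = 18 g of protein per day.

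**5. Nitrogen.** 1.35 / 6.25 = 0.216 and 1.5 / 6.25 = 0.24, so the printed nitrogen range follows the printed grams and repeats the 30-kcal basis. It is not independent evidence for them. The range matching 1.35–1.75 g/kg is 0.216–0.28.

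**The case against.** **The percentage is the rule and the grams only illustrate it.** The percentage is the main clause, and the grams and nitrogen follow as restatements. On that reading there is one incomplete conversion, with an upper end of 1.5 instead of 1.75, and not two rival rules. This is the more natural reading and it decides which correction to prefer. It does not make the printed conversion right, and the text never says that the grams apply at 30 kcal/kg/day only.

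**The energy factor is assumed.** The 33.3 threshold becomes 34.2 at 4.1 kcal/g and 35.0 at 4.2, where the zone with no valid intake disappears. But at 4.2, 18% of 30 kcal is 1.286 g/kg and 20% of 35 kcal is 1.667, so neither printed end is reproduced. The floor difference at 35 kcal/kg/day is still 1.50 − 1.35 = 0.15 g/kg. The caveat applies to the threshold and not to the mismatch.

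**Stronger readings that a reader might infer, and that the document does not support:**

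- *1.5 g/kg is a ceiling that sites would breach.* Nothing calls it a maximum or attaches a consequence to exceeding it. The intakes are planning targets, and the week-1 check looks for shortfall, so only the lower limit matters there.
- *The glutamine instruction is affected.* Where the dipeptide is added, "the amount of amino acids (or nitrogen) will be included in the calculated amount of protein intake". That counting works the same way under either figure.
- *The arms are treated unequally.* The protein rule is common to both. The week-1 check concerns the enteral arm only, but nothing in the document shows how often the choice of floor would change a decision, or that it would favor an arm.

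**Delivered intake will vary anyway.** The enteral rate is raised according to tolerance, and on the product, "The nutritional product will be the one usually used in each center". A condensed article may also leave working instructions to the full protocol. Both points limit the practical weight. Neither excuses two stated figures that disagree.

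**Conclusion.** The point holds as a minor numerical error in the dosing rule. The printed 1.35–1.5 g/kg/day is 18–20% of calories at 30 kcal/kg/day only; over the permitted range the percentage gives 1.35–1.75. That the ranges disagree follows from the ratio of their ends and needs no conversion factor. The gram values and the threshold of about 33.3 kcal/kg/day rest on 4 kcal/g, which the printed figures themselves imply at 30 kcal/kg/day. The nitrogen values rest on 6.25 g protein per gram.

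The consequence is an unclear protein floor, with a difference that grows from zero at 30 to 0.225 g/kg/day at 35 kcal/kg/day. Some intake meets both figures over the lower two-thirds of the calorie range, (33.3 − 30) / 5 = 0.67, although even there the floors differ above 30. The sample size and the primary analysis of 30-day closure do not use the figure and are unaffected.

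**What to change.** State one protein requirement, and use it both for planning the two arms and for the week-1 check.

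- **Preferred, because the percentage is the main clause:** keep 18–20% of caloric intake and restate the grams as 1.35–1.75 g/kg/day (nitrogen about 0.22–0.28 g/kg/day), adding that the value scales with the patient's calorie target.
- **Alternative, if the nutrition leads intended the gram range:** say that 1.35–1.5 g/kg/day (nitrogen about 0.22–0.24) governs, and restate the share as about 15–20% of calories over 30–35 kcal/kg/day.

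The choice is clinical. The cost is close to nil: a one-line correction or a clarification letter to sites, with no change to the design, sample size or analysis.

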### Data collection and follow-up

Follow-up of the patients will be at 30, 60, 90 and 180 days after randomization. The follow-up protocol includes a clinical examination (weight, temperature, arterial blood pressure), assessment of the status of fistula closure, paraclinic examination (CT scan with injection and ingestion of contrast product) for patients who do not show any output of fluid during 48 h in the wound or drainage, assessment of time to first fistula closure through the autoevaluation of fistula-associated symptoms questionnaire, laboratory tests (blood cell count, hemoglobin, white blood cell count with neutrophils, lymphocytes, monocytes, eosinophils, basophils, platelets, hematocrit, red blood cell count, aspartate transaminase, alanine aminotransaminase, alkaline phosphatase, γ-glutamyltransferase, total bilirubin, creatinine, C-reactive protein, serum albumin and prealbumin concentration, total protein, sodium, potassium, chloride, urea, glucose), nutritional assessment (weight, total protein, serum albumin and prealbumin concentration), a grip test for muscular strength measurement, assessment of the World Health Organization Performance Status, and quality of life questionnaires (36-item Short Form and EuroQoL five-dimensions questionnaire).

The study is planned to last 42 months, with a 36-month inclusion period and a 6-month follow-up period. The results of the primary end point will be available 30 days after the end of the inclusion period (3 years).

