## Methods/design

### Protocol overview

The NUTRILEAK trial is a multicenter, randomized, parallel-group, open-label, phase III study to assess the efficacy of EN compared to TPN in patients with PUGIF. After informed consent, patients will be randomized in a 2:1 ratio to the EN treatment arm and the TPN comparator arm. Patients will be randomized to receive EN through jejunostomy or nasojejunal tube, or to receive TPN through central venous access, a peripherally inserted central catheter line, totally implantable venous access or any other approved TPN device.

Any other surgical or endoscopic procedures aiming at directly closing the defect will not be allowed (including surgical closure and endoscopic clip, prosthesis or glue) throughout the whole study period. These measures have not been scientifically demonstrated to be efficient in this situation at this time and could be a confounding factor regarding our primary objective.

By contrast, surgical, radiological or endoscopic fistula drainage will be allowed throughout the whole study period. Any interruption of more than 24 h in the treatment determined by randomization (EN or TPN) will be reported, with the cause, duration and solutions given (i.e., the treatment provided or a switch to TPN in the EN group). During hospitalization, patients will be evaluated daily until fistula closure, with any fistula- or protocol treatment-related complication viewed through physical examination and, if required, through routine laboratory tests and/or imaging according to the usual practice of each center.

The present study protocol was written in compliance with the Standard Protocol Items: Recommendations for Interventional Trials (SPIRIT) 2013 [21]. A completed SPIRIT checklist is available as Additional file 1, and the schedule of this study is presented in Fig. 1.

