### End points

The primary end point is the fistula closure rate at 30 days after randomization. Fistula closure will be defined as no output fluid for 48 h in the wound or drainage and absence of any fluid collection on imaging (CT scan with contrast injection). The secondary end points are: 1) 6-month fistula closure rate; 2) time of first fistula closure, defined as time in days from randomization to first fistula closure within 6 months after randomization; 3) medical and surgical treatment-related complication rate at 6 months, including complications related to the nutritional support such as tube -related complications (dislodgment, infection, occlusion), venous catheter -related complications (thrombosis, infection), or any other nutritional route-related complications; 4) fistula-related complication rate at 6 months; 5) type and severity of early (before 30 days after randomization) and late (over 30 days after randomization) complications according to the Dindo–Clavien classification [22]; 6) mortality within 30 days and within 6 months after randomization; 7) nutritional status will be evaluated at day 30, day 60, day 90 and day 180 postrandomization based on weight, serum albumin and prealbumin concentration, C-reactive protein and grip test (muscular strength); 8) length of hospital stay in a health care structure (including home hospitalization) based on the cumulative number of days of hospitalization during the whole study period (from randomization until the end of the study); 9) patient health-related quality of life score based on the 36-item Short Form and EuroQoL five-dimensions questionnaires at inclusion and at days 30, 60, 90 and 180; 10) time from randomization to the oral diet covering at least 60% of the patient’s daily requirement ; 11) direct economic costs of therapy from a societal perspective, including the costs of hospitalization (inpatient and home settings), nutritional products, and early and late complications occurring during follow-up.

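### Time to first fistula closure is to be obtained from a patient symptom questionnaire, which cannot establish closure as the protocol defines it

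*Protocol article*

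**What the plan says.** The End points section of the protocol article gives one definition of the event: "Fistula closure will be defined as no output fluid for 48 h in the wound or drainage and absence of any fluid collection on imaging", the imaging being a contrast CT. In the same section, secondary end point 2 is "time of first fistula closure, defined as time in days from randomization to first fistula closure within 6 months after randomization". It carries no definition of closure of its own, so the general one applies.

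The Data collection and follow-up section sets the visits: "Follow-up of the patients will be at 30, 60, 90 and 180 days after randomization". Among the visit procedures it lists three separate items that bear on closure:
- an assessment of closure status;
- a CT, restricted to patients whose output has stopped for 48 hours;
- for the timing of closure, the entry "assessment of time to first fistula closure through the autoevaluation of fistula-associated symptoms questionnaire".

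The questionnaire is attached only to the third item, the time.

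The Protocol overview describes the trial as open-label and adds: "During hospitalization, patients will be evaluated daily until fistula closure". It does not say that this daily evaluation supplies the date for end point 2.

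**The concern.** The event and the instrument that is to date it do not match. Closure is defined by output and imaging, but its time is to come from what patients report about their symptoms. Symptoms are not the output criterion, and no self-report can show the absence of a collection on CT. Status and date therefore come from different sources. A patient could be dated as closed by questionnaire while the CT still shows a collection, or meet both objective criteria on a day that the questionnaire does not reflect.

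Two features make this more than untidy wording. First, the Background gives the aim as showing that enteral nutrition speeds healing, and time to first closure measures speed most directly. Second, patients know how they are being fed, so error in a self-reported date could differ between arms. The documents do not indicate in which direction.

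This is not a detail left to the full protocol or the statistical analysis plan. The article names the instrument, and the instrument named does not fit the definition.

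**Working it through.** **Step 1. Definition against measurement.**

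| Element | End points section | Data collection and follow-up section |
|---|---|---|
| Closure status | 48 h without output, and no collection on contrast CT | Status assessed at visits; CT if no output for 48 h |
| Time of first closure | Days from randomization to that event | Patient self-assessment of fistula-associated symptoms |

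The first row agrees across the two sections. The second does not.

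**Step 2. Reproduce the plan's own figure, to see what is unaffected.** The inputs, from Statistical evaluation and sample size, are closure rates of 35% (TPN) and 55% (EN), two-sided alpha 0.05, power 90%, 2:1 allocation and a 10% allowance for 30-day mortality. With pooled variance under the null and no continuity correction:

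- p̄ = (0.35 + 2 × 0.55)/3 = 0.4833
- n(TPN) = [1.960 × √(1.5 × 0.4833 × 0.5167) + 1.282 × √(0.35 × 0.65 + 0.55 × 0.45/2)]² / 0.20² = 95.95, rounded up to 96
- n(EN) = 2 × 96 = 192
- With the mortality allowance: 96/0.9 = 106.7, rounded up to 107 TPN; 2 × 107 = 214 EN; total 321

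This matches the stated 321 exactly. The calculation concerns the 30-day closure proportion and does not use the date of closure. No figure is stated for time to first closure.

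**Step 3. Closures expected by day 30 at the planning rates.**

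- Rates applied to the patients left after the mortality allowance: 0.35 × 96 + 0.55 × 192 = 33.6 + 105.6 = 139.2, about 139
- Rates applied to all randomized patients: 0.35 × 107 + 0.55 × 214 = 37.5 + 117.7 = 155.2, about 155

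So about 139 to 155 closure dates fall before the first follow-up visit. This counts early closures, not recalled dates.

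**Step 4. Longest possible delay between closure and report.** The questionnaire's schedule and recall period are not given. If it is completed only at the follow-up visits, the gaps are 30 − 0 = 30, 60 − 30 = 30, 90 − 60 = 30 and 180 − 90 = 90 days. A closure could then be reported up to 30 days later (to day 90) or up to 90 days later (days 90 to 180). These are maximum gaps, not estimates of error.

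**The case against.** The strongest reply is that contemporaneous information on closure will exist anyway. Hospitalized patients are evaluated daily until closure. Under Treatment methods, nil-per-mouth lasts until at least 5 days after closure, so staff must judge closure as it happens, at least in hospital. A CT is also triggered by 48 hours without output. In addition, a journal article commonly leaves the questionnaire's content, schedule and recall period to the full protocol.

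Much of this stands. A reader might infer that every closure before day 30 would be dated from memory at the first visit. The documents do not support that: many of these closures may occur in hospital under daily evaluation, and the number after discharge is not given. Nor do 30 and 90 days measure the actual error. They are visit gaps under an assumed completion schedule, and recall and arm-dependent bias are themselves inferences.

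A reader might also infer two incompatible definitions of closure from the CT wording, since End points mentions contrast injection and the follow-up section has "CT scan with injection and ingestion of contrast product". The shorter description does not exclude oral contrast, and both sections apply the same 48-hour output criterion together with CT. This is a difference in detail, and the point does not rest on it.

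The reply does not remove the mismatch. No section links the daily evaluation to end point 2, and the one source named for its timing is the questionnaire.

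**Conclusion.** The point holds for secondary end point 2. The stated source for the date of first closure conflicts with the protocol's definition of closure, so date and status can disagree, and an open-label self-report may be biased by arm. The conflict is plain from the text and rests on no assumption.

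Its effect on the results cannot be quantified from the documents. It depends on how many closures occur after discharge and on how the questionnaire is administered, and neither is given.

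A reader might extend the concern to the main result. That is not supported: closure status and CT are listed separately from the questionnaire, and the primary objective is the 30-day closure rate. The primary end point, its definition and the total of 321 are untouched. The correction should be made, because this end point bears directly on the stated aim and the better source is already planned.

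**What to change.** Reconcile Protocol overview, End points, and Data collection and follow-up as follows.

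1. State that the date of first closure for end point 2 follows the End points definition, for example the first day of the 48-hour output-free period that is later confirmed by CT.
2. Name its source: the daily evaluation while the patient is in hospital and, after discharge, wound or drain output records together with the CT.
3. Treat closures first detected at a follow-up visit as interval-censored between the last assessment without closure and that visit.
4. Keep the symptom questionnaire as supportive information only.

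The cost is wording and one date field in the eCRF. The daily evaluation and the triggered CT are already planned, and the sample size does not change.
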